## Abstract

**Background:**

Chronic prostatitis otherwise known as chronic pelvic pain syndrome is a common urological diagnosis that causes many men significant morbidity and has a detrimental effect on their quality of life. Standard treatment with antibiotics and simple analgesia are often ineffective and many patients are managed by the chronic pain services.

Cognitive behavioural therapy has been shown to be helpful in the management of many chronic diseases and has recently been proposed as an effective treatment for chronic prostatitis. Furthermore, a self management programme administered to groups of men with lower urinary tract symptoms has been shown to be more effective than standard treatments including surgery.

Therefore, we have developed a cognitive behavioural therapy programme specifically for men with chronic prostatitis. This novel treatment approach will be compared to conventional therapy in the pain clinic such as atypical analgesia and local anaesthetic injections in the context of a randomised controlled trial.

**Methods/Design:**

Men will be recruited from general urology outpatient clinics following the exclusion of other diagnoses that could be responsible for their symptoms. Men will be randomised to attend either a self management healthcare and education programme or to pain clinic referral alone. The self management programme will be administered by a clinical psychologist to small groups of men over six consecutive weekly sessions each lasting two hours. Patients will be taught techniques of problem-solving and goal-setting and will learn coping mechanisms and how to modify catastrophic cognition.

The primary outcome will be change from baseline in the National Institute of Health Chronic Prostatitis Symptom Index, a validated instrument for the assessment of men with chronic prostatitis. Secondary outcomes include generic quality of life scores and analgesic and drug usage. Outcomes will be assessed at 2, 6 and 12 months.

**Discussion:**

If this group administered self management programme is shown to be effective in the treatment of men with chronic prostatitis it may become the new standard of care for these patients. Furthermore, it may be adapted for use in women with interstitial cystitis, a condition which is analogous to chronic prostatitis in men.

**Trial Registration:**

Current Controlled Trials ISRCTN21012555

## Background

Prostatitis is a common urological diagnosis in men of all ages, representing 8% of male urology office visits [1]. Type III prostatitis, also referred to as chronic prostatitis/chronic pelvic pain syndrome (CP/CPPS) is the most common type and accounts for 90-95% of prostatitis diagnoses [2].

Standard care for men with CP/CPPS has traditionally consisted of initial assessment by a urological surgeon to exclude an underlying reversible organic cause for pain, followed by a non-uniform pathway that incorporates a variety of pharmacological approaches including antibiotics, non-steroidal anti-inflammatory drugs, alpha-adrenoceptor blockers, 5-alpha-reductase inhibitors and specialist pain-clinic approaches such as the use of gabapentin. That no one therapeutic approach is consistently beneficial underpins the fact that the underlying condition is multifactorial in its pathogenesis and includes physical, emotional and psychological components [3]. Effective treatment, therefore, must focus not only on the physical pathology but also the emotional and psychological aspects of the disorder. Psychosocial factors were recently targeted in the development of a cognitive-behavioural programme designed specifically for men with CP/CPPS [4]. Furthermore, a recent analysis of the large National Institute of Health Chronic Prostatitis Cohort showed that psychological variables could predict pain experience [5].

Self management interventions that enhance patients' problem solving and goal-setting skills have been shown to be effective for a number of chronic diseases including arthritis, diabetes and asthma through reduction in secondary care referrals, reduced primary care attendance and increased self efficacy [6]. More recently a group-directed self management programme has been shown to improve both symptoms and quality of life in men with lower urinary tract symptoms attributed to benign prostatic hyperplasia [7].

We have developed a programme of cognitive behavioural therapy for men with CP/CPPS. This intervention uses personal health planning and self directed care delivered in the context of small group sessions. We believe that through this holistic approach we can improve these patients' quality of life and functional status, reduce their pain and reduce the need for sustained primary and secondary care consultation.

The main objective of the study is to show that our programme of group-directed cognitive behavioural therapy for men with CP/CPPS is more effective than standard therapy (pain relief and coping mechanisms delivered in the pain clinic).

## Methods/Design

### Study Design

We believe that our self management programme would be best evaluated in the context of a randomised controlled trial compared to standard care. A randomised controlled trial is the most rigorous trial design that will allow comparison of the effectiveness of our intervention with standard treatment and will also allow an economic evaluation.

### Setting

The trial will take place at the Norfolk and Norwich University Hospital NHS Foundation Trust. The treatment sessions will take place at the Pain Management Centre and follow-up visits will be scheduled in the hospital outpatient department.

### Patients

We will recruit men with CP/CPPS that has not responded to simple treatment with painkillers or antibiotics from general urology outpatient clinics at Norfolk and Norwich University Hospital NHS Foundation Trust. All patients aged 18 or over with CP/CPPS referred for the first time by their GP will be eligible for inclusion. All patients will be assessed by a consultant urologist to diagnose CP/CPPS and exclude other important causes for their symptoms (for example, ureteric stones, prostate cancer).

Patients meeting these inclusion criteria will be offered the opportunity to take part in the study. Those who do not wish to take part will be offered standard care and be referred to the pain clinic if they wish.

If during the course of the study it becomes clear that further psychological treatment would be required for an unexpected diagnosis in a given participant, this would be made available.

Vulnerable patients, those who are unable to consent for themselves and patients who do not speak English will be excluded from the study. A detailed and explicit list of inclusion and exclusion criteria is provided in Table 1.

**Table 1 T1:** Inclusion and Exclusion Criteria

*Inclusion Criteria*
• Men
• Age 18 years or order
• Diagnosis of Type III chronic prostatitis/chronic pelvic pain syndrome by a consultant urologist
• Failure of simple analgesia and antibiotics to control symptoms
*Exclusion Criteria*
• Prostate cancer or suspected prostate cancer
• Renal tract calculi
• Acute bacterial prostatitis
• Other urological and non-urological diagnoses that could account for a patient's symptoms
• Inability to comprehend and converse in the English language
• Vulnerable adults

A comprehensive list of the study inclusion and exclusion criteria.

### Power Calculation

This is based on the primary outcome measure, the National Institute of Health Chronic Prostatitis Symptom Index (NIH-CPSI, see Figure 1). Mean NIH-CPSI scores in published trials are around 25, with standard deviation in the region 6-7. To detect a mean fall in NIH-CPSI of 4 points, we used CPSI score in control of 25.2, and CPSI score of 21.2 in the intervention with standard deviations of 6.1 and 7.2 in the control and intervention respectively. At 90% power, 5% two sided significance level, we estimate a sample size of 59 individuals in each group. Taking account of 15% loss to follow-up, we will require 60 individuals in each group giving a total sample size of 120.

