### Statistical analysis

First descriptive and demographic statistics will be presented at baseline and follow-up measurements including measures of locations, for example mean or median and measures of spread including standard deviations or interquartile range depending on the distribution of measurements. Further, percentages and the 95% confidence intervals will be given for categorical data stratified by treatment group. All statistical tests will be carried out using two-sided tests at 5% significance level.

Given the repeated nature of our study, we will use the analysis of covariance approach recommended by Frison and Pocock for which the follow-up measurements are analysed at each follow-up time point adjusting for baseline and other confounding factors [9].

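### Sixty men per group does not allow for 15% loss to follow-up: it leaves 51 evaluable per group and about 85–86% power, not 90%, for the unadjusted comparison on which the trial was sized

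*Protocol article*

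**What the plan says.** The Power Calculation section sizes the trial on the primary outcome, the NIH-CPSI score. It assumes mean scores of 25.2 under control and 21.2 under the intervention, a difference of 4 points, and takes "standard deviations of 6.1 and 7.2 in the control and intervention respectively". From these it concludes: "At 90% power, 5% two sided significance level, we estimate a sample size of 59 individuals in each group". The next sentence gives the recruitment target: "Taking account of 15% loss to follow-up, we will require 60 individuals in each group giving a total sample size of 120".

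The target of 60 and 120 is used elsewhere in the article. Table 4 (Resource Requirements) costs therapy rooms and refreshments for 60 participants and assessment rooms for 120, and budgets consultant time at one hour for each of 120 participants. So 60 per group is the operative figure and not a misprint of a larger one.

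The Statistical analysis section plans an analysis of covariance in which "the follow-up measurements are analysed at each follow-up time point adjusting for baseline and other confounding factors". The Power Calculation section mentions neither this adjustment nor any correlation between baseline and follow-up scores.

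**The concern.** An allowance of 15% should raise a requirement of 59 by roughly ten men per group. Here it raises it by one. Either the 59 already contains the allowance, or the allowance was never applied. If it was never applied, the power statement does not follow from the plan's own inputs.

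What is at stake is how the result is read. Follow-up runs to 12 months and the plan itself expects 15% of men to be lost. A null result would be taken as coming from a trial with 90% power after attrition, and the stated calculation does not support that. Type I error and bias are not affected.

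**Working it through.** **Inputs, all from the Power Calculation section**

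- Difference in means: 25.2 − 21.2 = 4 points
- Standard deviations: 6.1 (control) and 7.2 (intervention)
- Two-sided 5% significance (z = 1.960) and 90% power (z = 1.2816)
- Loss to follow-up: 15%
- Equal groups, as the Randomisation methods section also implies

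**Step 1. Reproduce the 59.**

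n per group = (1.960 + 1.2816)² × (6.1² + 7.2²) / 4²

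= 10.507 × (37.21 + 51.84) / 16 = 10.507 × 89.05 / 16 = 58.48, rounded up to **59**.

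This matches the plan. Power with 59 evaluable men per group is 90.2% (normal approximation) or 89.8% (t-test). The 59 therefore contains no dropout allowance.

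**Step 2. Apply the 15% loss.**

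- Standard inflation: 59 / (1 − 0.15) = 69.4, so **70 per group, 140 in total**.
- Weaker inflation that is sometimes used: 59 × 1.15 = 67.85, so 68 per group, 136 in total.
- Loss that 60 per group can absorb while keeping 59: 1/60 = **1.7%**.

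Other conventional settings do not explain 60 either. A one-sided 5% test at 90% power needs 48 per group before loss, and a two-sided test at 80% power needs 44. Neither is the stated design.

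**Step 3. Power at the stated target after the stated loss.**

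- Evaluable per group: 60 × 0.85 = **51**
- Standard error of the difference: √(89.05 / 51) = 1.321
- Power (normal) = Φ(4 / 1.321 − 1.960) = Φ(1.067) = **85.7%**
- Power (noncentral t, pooled or Welch) = **85.0%**
- Type II error: 14–15% instead of 10%
- Difference detectable at 90% power: 3.2415 × 1.321 = **4.28 points**

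**Step 4. What the planned covariance analysis could recover.**

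Assume that adjusting for baseline multiplies the variance in both groups by (1 − r²), where r is the correlation between baseline and follow-up scores. The article gives no r, so a range is shown for 51 evaluable men per group.

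| Assumed r | Power (normal) | Power (t) |
|---|---|---|
| 0.2 | 87% | 86% |
| 0.3 | 89% | 88% |
| 0.4 | 91% | 90.5% |
| 0.5 | 94% | 93% |
| 0.6 | 97% | 96% |

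The correlation at which 51 per group does the work of the full requirement is √(1 − 51/58.48) = 0.358, or √(1 − 51/59) = 0.368 using the rounded figure. With the t distribution it is about 0.38 (r = 0.37 gives 89.7%).

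**The case against.** The strongest reply is that the 85–86% belongs to an analysis the trial will not carry out. The planned analysis adjusts for baseline, and sizing on an unadjusted comparison before analysing by covariance is generally conservative. With a correlation of 0.4 or more, 51 men per group give at least 90% power. This stands as a limit on the conclusion: the power of the planned analysis has not been shown to fall short of 90%. Nor is the difference between the sizing method and the analysis method a second error; it is the main mitigating factor. But it does not make the statement true. The section compares two follow-up means, does not invoke the adjustment to justify 60, and states no correlation.

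A second reply is that the effect is modest: 4 to 5 points of power and 0.28 points in the detectable difference. That is fair. The trial is not invalidated.

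Two smaller points also stand. First, the article does not say at which of the 2-, 6- and 12-month visits the 15% applies, so 51 is exact only where the full loss has accrued. Second, the 86% ignores any clustering from delivering the intervention in groups of 5–8 men. Assume five evaluable men per therapy group and an intra-class correlation of 0.01 to 0.05 in the intervention arm only. The intervention variance is then multiplied by 1 + 4 × ICC, and unadjusted power at 51 per group (normal approximation) is about 85% falling to 82%. That makes the shortfall worse, so it does not rescue the statement.

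**Conclusion.** The concern holds. The claim that 60 per group takes account of 15% loss is wrong on the plan's own figures. The 59 is the uninflated requirement, the correctly inflated number is 70 per group, and 60 leaves 51. For the unadjusted comparison used in the calculation, power is 85.7% (normal) or 85.0% (t), and 90% power is reached at 4.28 points, not 4.

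These figures rest on the stated standard deviations, the full 15% loss in each group and no clustering. Under the planned covariance analysis the 90% may still be met, but only with a baseline-to-follow-up correlation of about 0.36–0.38 or more, which the article neither states nor supports. Nothing elsewhere in the article repairs the step, and the costing confirms 60 and 120 as the working numbers.

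**What to change.** Correct the paragraph and remove the claim that 60 per group allows for 15% loss. Either of two versions keeps the total at 120:

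1. **Restate the power.** Sixty men per group will be randomised. After 15% loss, 51 per group are evaluable, giving about 86% power for a 4-point difference, or 90% for 4.3 points, in an unadjusted comparison that ignores clustering by therapy group.
2. **Keep 90% on the planned analysis.** Base the calculation on the baseline-adjusted analysis, state the assumed correlation between baseline and follow-up scores (at least 0.37 by the normal approximation, about 0.38 by the t distribution), and give its source.

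In either version, say at which visit the 15% loss is assumed. Raising the target to 70 per group would also restore 90% for the unadjusted comparison. It is optional and would add 140 − 120 = 20 men and their costs.

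The first two versions cost one corrected paragraph and no extra patients. The first also means a slightly less favourable power figure, and the second needs a defensible correlation.

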**Figure 1 F1:**
[figure not shown]
**NIH-Chronic Prostatitis Symptom Index**. The National Institutes of Health Chronic Prostatitis Symptom Index, a validated questionnaire for the assessment of men with CP/CPPS. It evaluates pain and urinary symptoms, and assesses the impact of the condition on function and quality of life.

### Randomisation methods

Randomisation will be carried out by a method of Random Permuted Blocks so as to ensure exact equal treatment numbers at certain equally spaced time points in the sequence of patient assignments. The randomisation sequence will be generated using statistical software in random blocks, size of four individuals per block.

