### Data Collection, Management and Analysis

Data will be collected and managed by a Specialist Research Nurse. The Specialist Research Nurse will be responsible for the day-to-day running of the trial as well as the collection of all administrative, demographic and outcome data. She will be the key contact for participants requiring support or advice throughout the study.

Outcome data will be collected at the time of enrolment into the study and again at 2, 6 and 12 months reviews after the commencement of treatment as part of a routine outpatient pain clinic review. The Specialist Research Nurse responsible for collecting these data will not be aware which treatment each patient has received.

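### The fixed, published block size of four would make on average a third of allocations certain in advance to anyone who can see the earlier ones

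*Protocol article*

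**What the plan says.** Under Randomisation methods, the Protocol article chooses random permuted blocks and gives the size: "The randomisation sequence will be generated using statistical software in random blocks, size of four individuals per block". The stated purpose is "so as to ensure exact equal treatment numbers at certain equally spaced time points in the sequence of patient assignments". Equality at equally spaced points is possible only if every block has the same length, so the word random describes the order within blocks and not their size.

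The setting is one hospital trust (Setting: "The trial will take place at the Norfolk and Norwich University Hospital NHS Foundation Trust"), and no stratification is mentioned. Allocation is 1:1 (Power Calculation: "we will require 60 individuals in each group giving a total sample size of 120"). The arms are described in the abstract: "Men will be randomised to attend either a self management healthcare and education programme or to pain clinic referral alone".

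Under Data Collection, Management and Analysis, the research nurse is "responsible for the day-to-day running of the trial as well as the collection of all administrative, demographic and outcome data". The same section says: "The Specialist Research Nurse responsible for collecting these data will not be aware which treatment each patient has received". The article does not say who enrols men, who holds the list, or who sees past assignments.

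**The concern.** With one constant, known block size and one sequence, the end of each block follows from its beginning. The fourth man's arm is always determined. After two men in a row at the start of a block go to the same arm, the third man's arm is determined as well. The block size is in print, so the only other thing needed is sight of the earlier allocations in order.

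The arms differ visibly: one man joins weekly group sessions and another does not. Recruitment of 10-12 men a month (timetable under Study Plan) fills only 2.5 to 3 blocks a month, which is easy to follow.

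What is at stake is selection bias. Someone who knows the next arm could, even without intent, let the timing of enrolment or a borderline eligibility judgement depend on it. The primary outcome is a patient-completed symptom index, so differences between arms in expectation or willingness to engage could reach it directly. Analysis cannot reliably repair that afterwards.

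**Working it through.** The article gives no figure for predictability, so there is none to reproduce. Its block size and total do agree with each other: 120 / 4 = 30 blocks, each with 2 men per arm, and 30 × 2 = 60 per group.

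**Inputs.** Block size 4, constant (Randomisation methods); 1:1 allocation and 120 men (Power Calculation); one sequence (one centre under Setting, no stratification mentioned). Assumption not in the article: the observer sees all earlier allocations in order.

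**Allocations known with certainty.** An allocation is certain once one arm's two places in the block are used up. There are six equally likely orders.

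| Orders | Number | Certain allocations per block |
|---|---|---|
| AABB, BBAA | 2 | 2 (third and fourth) |
| ABAB, ABBA, BABA, BAAB | 4 | 1 (fourth) |

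- Mean per block: (2 × 2 + 4 × 1) / 6 = 8/6 = 4/3.
- Share: (4/3) / 4 = 33.3%.
- Over 30 blocks: 30 × 4/3 = 40 of 120 men.
- Minimum 30 × 1 = 30 (25%); maximum 30 × 2 = 60 (50%).

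**Best guess.** The observer always guesses the arm with more places left, or tosses a coin when they are level.

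- First man: 1/2.
- Second man: 2/3.
- Third man: certain with probability 1/3, otherwise a coin toss, so 1/3 × 1 + 2/3 × 1/2 = 2/3.
- Fourth man: 1.
- Mean: (1/2 + 2/3 + 2/3 + 1) / 4 = 17/24 = 70.8%.

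**Alternatives, for the same observer.** Fixed sizes were enumerated. Mixed sizes were simulated (2,000 sequences of 120), with sizes equally likely and the observer assumed to know the set of sizes but not the order in which they occur.

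| Scheme | Certain in advance | Of 120 men | Best guess right |
|---|---|---|---|
| Fixed 4 | 33.3% | 40 | 70.8% |
| Fixed 6 | 25% | 30 | 68.3% |
| Fixed 8 | 20% | 24 | 66.6% |
| Random 4/6 | 5.5% | about 7 | 69.2% |
| Random 4/6/8 | 2.2% | about 3 | 67.9% |

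Random sizes remove most of the certainty, because the observer no longer knows where a block ends. They barely change the guess rate.

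**Price in balance.** If recruitment stops at 120 inside a block of 8, the largest possible difference is 4 men, 62 against 58. The variance factor is then 1/62 + 1/58 = 0.03337, against 2/60 = 0.03333, an increase of about 0.1%.

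**The case against.** A reader might infer that recruiting staff will know a third of allocations in advance. The article does not support this. It never says that recruiters see earlier assignments, and if they do not, the share known is 0% and a guess is right half the time, even with blocks of four. The trial is not called open-label; that is a sound inference for patients and therapists only. For the research nurse the article states the opposite of access: she will not know the treatment received. Her other duties make this hard to sustain, since she runs the trial, handles all administrative data and is the participants' key contact, but that is doubt about a safeguard and not evidence of foreknowledge.

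Nor may one infer that concealment is lacking. A condensed article may leave the custody and release of the list to the full protocol, so silence on it is no finding.

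There are also safeguards on paper. All first-referral men with the condition are eligible, a consultant urologist makes the diagnosis, and men who meet the criteria are offered the trial (Patients). The analysis adjusts for baseline and other confounding factors, and the patient activation measure, SF-36 and HAD scale are collected at baseline (Study Plan). These limit the room for steering and might absorb some of its effect. They do not remove the point, because the covariates are not named and adjustment cannot be relied on for unmeasured selection.

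Finally, setting 71% against 50% would oversell the remedy: an observer with access would still guess right about 68-69% of the time. What stands is the stated choice of a small, constant and disclosed block size.

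**Conclusion.** The point holds in conditional form. The constant block of four is a weak choice that the article states, not something it leaves out. For anyone able to see earlier allocations in order, it makes one third of allocations certain on average (about 40 of 120, range 30 to 60) and a best guess right about 71% of the time. This rests on 1:1 allocation, one unstratified sequence and that access; the first is stated, the second follows from one centre with no stratification mentioned, and the third is not established. No size of bias on the symptom index can be derived from the article. The change is worth making because it is cheap and lowers the risk even if masking of past allocations fails.

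**What to change.** Replace the fixed block of four with randomly varying block sizes, for example 4, 6 and 8, and state that the sizes are not disclosed to recruiting staff. Drop the promise of equal numbers at equally spaced points, which varying sizes cannot keep. Possible wording: *Allocation will be 1:1 in permuted blocks of randomly varying size; the sizes will not be disclosed to staff who recruit or enrol participants.* The set of sizes then belongs in a restricted document and not in the published text.

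For an observer who sees past allocations and even knows the set of sizes, this lowers certain foreknowledge from 33.3% to about 2.2% (about 5.5% with 4 and 6 only). The remaining guess rate of about 68-69% can be brought down to 50% only by keeping earlier allocations from recruiters, so the two measures complement each other.

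The cost is a setting in the randomisation program and one or two protocol sentences. The downside is a possible final imbalance of up to 4 men with sizes 4, 6 and 8, with negligible effect on power.
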